### Inclusion and exclusion criteria

The patients must meet all of the following inclusion criteria at the time of enrollment
Must be scheduled for a pancreatoduodenectomyMust be ≥ 18 yearsMust be able to give written, signed, and informed consentThe Investigator must ascertain that the patient is able to understand, comply and follow the instructions needed to successfully participate in this trial

The following must not be present at the time of enrollment
Allergy to the perfusion fluid Voluven® (Fresenius Kabi AS, Halden, Norway)Allergy to the contrast agent given during CT scanAny medical- or other condition that the surgeon deems sufficient to make the patient unfit for participation in the trialParticipation in other interventional clinical studies interfering with the current studyPregnantAny infectious disease that makes microdialysis analysis impossible to carry outNo inclusion/exclusion criteria for the surgeon exist.

### Design, enrollment, inclusion, and randomization

The MINIMUM study is a 2-armed, single-center, randomized, parallel-group trial with an equivalence framework. The study population is patients scheduled for open pancreatoduodenectomy at Oslo University Hospital – Rikshospitalet, Norway. This center normally performs 130 open pancreatoduodenectomy each year and MINIMUM seeks to enroll 200 consecutive patients scheduled for open pancreatoduodenectomy. Half of the included patients (intervention group) will be randomized to receive an intraperitoneal microdialysis catheter inserted at the end of surgery and will postoperatively be monitored by microdialysis. The surgeon will have full access to the microdialysis results at any time during the study period. The surgeon may intervene based solely on the patient’s symptoms and signs, plus predetermined values of the microdialysis measurements. The other half of the patients (control group) will not receive a microdialysis catheter. The patients are monitored according to the current standard of care and the surgeon may intervene based only on symptoms and signs. The only difference between the two groups is that the treating surgeon in the intervention group will implant a microdialysis catheter close to the pancreaticoenterostomy. Once implanted, the microdialysis results will be available to the treating team, and these results can be included into the assessment and management of the patient. Group assignments will be determined by an online randomization system; (Viedoc™) developed by PCG Solutions ([name]). Screening and enrollment of patients will be performed by the investigators. All the patients will be included minimum 1 day prior to surgery. The study will be conducted according to the Helsinki declaration. A special combined patient information leaflet and consent form has been developed for the MINIMUM study. Patients will be recruited from the operation planning program on site. After informed consent has been obtained by the principal investigator or co-investigator, the patients will be included. The trial will be conducted in accordance with the Consolidated Standards of Reporting Trials (CONSORT) Statement.

The study has been approved by the institutional review board of Division of Emergencies and Critical Care, Oslo University Hospital, the regional ethics committee in Norway (Regional Committees for Medical and Health Research Ethics – Additional files 3 and 4) and has been registered at clinicaltrials.gov (NCT03631173). Insurance policies for all patients are obtained by the Norwegian National System of Patient Injury Compensation.

### Blinding

In this study, there will be no blinding of the patients or the health care providers in regards to the microdialysis catheter or the results from the bedside microdialysis results. The group affiliation is obvious for the different caregivers because of the highly visible microdialysis catheter and frequent analyses of the microdialysate.

### Participant timeline

Randomization started in April 2019 at Oslo University Hospital and will last for 2 years. The Assessment Schedule is presented in Table 2.

**Table 2 Tab2:** Assessment Schedule

	Study period						
Event	Pre-admission	Pre-operative	Intra-operative	Post-operative			
				During admission	At discharge	30th POD	90th POD
**Eligibility screen**	≥ 1 day prior surgery						
**Information - signed informed consent**	≥ 1 day prior surgery						
**Inclusion**	X						
**Randomization**			X				
**Intervention - microdialysis**			X	X			
**Control (standard care)**			X	X			
**Start eCRF**	X						
**Premedication**		X					
**Epidural**		X					
**Arterial catheter**		X					
**Central venous line**		X					
**Targeting anesthesia**			SpO_2_ ≥ 93%. BPmap ≥ 60 mmHg. Body temperature ≥ 36 °C. Ventilatation with 6–8 ml/kg PBW				
**Pantoperazole 40 mg iv**				Administered daily for 7 days			
**Assessments**							
**Patient characteristics**	Gender, age, height, weight, BMI, blood pressure, heart rate, SpO2						
**SOFA-score**	X			Daily until POD 10 if applicable			
**Weight loss last 6 months**	X						
**Concomitant medication**	X						
**Smoking history**	Current, pack years						
**Medical history**	Including pancreatitis						
**Preoperative chemotherapy**	X						
**Preoperative CT scan**		X					
** Intraabdominal fat thickness**		X					
** The relation to portal vein to tumor**		X					
** Width of pancreatic duct**		X					
** Width of pancreas**		X					
** Current diseases**	Histology – differentiation of tumors and TNM staging	X					
**Quality of life questionnaire - Abdominal surgery Impact scale**	> 1 day before surgery. After inclusion but before randomization			POD 3	X	X	X
**Short-form McGill Pain Questionnaire-2 (SF-MPQ-2)**	> 1 days before surgery. After inclusion but before randomization			POD 3	X	X	X
**Blood samples**	Hb, Trc, WBC, ASAT, ALAT, GGT, ALP, LD, Amylase, Bilirubin, Creatinine, Urea, GFR, CRP, a panel of inflammatory markers, s-lactate, and arterial blood gas.			Daily at 08.00 am: Hb, Trc, WBC, Amylase, ASAT, ALAT, GGT, LD, ALP, Bilirubin, Creatinine, GFR, UREA, CRP, a panel of inflammatory markers, s-lactate, arterial blood gas.			
**iv fluid**			X				
**Urine output**			X				
**Blood loss**			X				
**Transfusion**			X	X			
**Use of vasoactive medicaments**			X				
**Intraoperative PD width**			X				
**Intraoperative pancreatic consistency**			X				
**Histological assessment**							
**Pancreatic fat**			X				
**Pancreatic fibrosis**			X				
**Drain tube**			Insertion	Cessation POD 1–3 (or more) unless the effluent is bile, enteric stained or turbid or depending on microdialysis concentrations			
**Amylase and bilirubin in drain fluid**				At POD 1–3 and on indication thereafter if drain still in place			
**Pantoperazole 40 mg iv**				Administered daily for 7 days			
**Sampling/analyzing microdialysate**				Every hour in the first 24 h. Thereafter, every two hours until POD 2. From POD 2: every 4th hour until discharge; Pyruvate, lactate, glucose, glycerol			
**Collecting microdialysate for cytokines**				Twice daily (≈ 08.00 am and 08.00 pm)			
**Microdialysis catheter function and duration**			X	X			
**Abdominal CT scan during admission(s)**				POD 2 in patient with high microdialysate concentrations in three consecutive microdialysate samples and/or at the surgeon's discretion	at the surgeons discretion	at the surgeons discretion	at the surgeons discretion
**Postoperative complications - Clavien-Dindo classification ≥ 2**				X	X	X	X
**Time from end of surgery to a diagnosed anastomosis leakage, if applicable**				X	X	X	X
**Type of complications**				X	X	X	X
**Type of procedures due to complications**				X	X	X	X
**Cost of complications**				X	X	X	X
**Transfer(s) to ICU**				X	X	X	X
**LOS at primary hospital and ICU**				X	X	X	X
**LOS at secondary hospital**						X	X
**Mortality**			X	X	X	X	X

*ALAT* alanine aminotransferase, *ALP* alkaline phosphatase, *ASAT* aspartate aminotransferase, *BMI* body mass index, *CRP* c*-*reactive protein, *CT* computed tomography, *GFR* glomerular filtration rate, *GGT* gamma*-*glutamyl transferase, *Hb* hemoglobin, *ICU* intensive care unit, *LD* lactate dehydrogenase, *LOS* length of stay, *PBW* predicted body weight, *PD* pancreatic duct, *POD* postoperative day, *SpO2* peripheral oxygen saturation, *TNM* tumor-nodule-metastasis, *Trc* platelets, *WBC* white blood cells

### Miscellaneous data to be collected

All data will be plotted in a password-protected web-based eCRF (Viedoc™, PCG Solutions, [name]) consecutively by the study team (investigators and study nurses).

Baseline demographic data, current medication, and the presence of any chronic diseases will be collected. Intraoperative data and postoperative complications, as defined by the modified Clavien-Dindo classification, will be recorded until POD 90. Total hospital stay + LOS at the hospital/ICU, pre- and postoperative CT-scan results, mode of nutrition, and any transfusion requirements will also be recorded. Sequential Organ Failure Assessment scoring (SOFA) will be performed preoperatively, and up to POD 10 if the patient is still admitted at the primary hospital. Also, the investigators will calculate the financial burden related to ICU stay, inpatient stay at the hospital, readmissions, reoperations, and (expensive) treatment procedures and examinations performed as a consequence of a POPF-development.

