## Background and rationale

### Pancreatoduodenectomy and postoperative pancreatic fistula (POPF)

Pancreatoduodenectomy is the treatment of choice for tumors of the periampullary region. Due to its high-risk nature, pancreatoduodenectomy has become a routine procedure in specialized high-volume centers, and mortality has decreased significantly over the last decades. To achieve better results, several factors have been identified and improved upon; pre-and postoperative management, appropriate selection of patients, improved surgical tools and skills, and the development of multidisciplinary teams [1, 2]. However, even if mortality is less than 3–5% in experienced hands, the overall morbidity rate is still high—from 30% to 50%—leading to prolonged in-hospital stay and increased costs [3]. There are 3 different anastomoses (surgical connection between two structures) with the potential for a leak post-pancreatoduodenectomy; the gastrojejunostomy, choledochojejunostomy, and the pancreaticojejunostomy. An anastomotic leakage after pancreatoduodenectomy is a feared complication with substantial mortality and morbidity. Formation of a postoperative pancreatic fistula (POPF) is a serious complication. Pancreatic secretions with its eroding enzymes like proteases and lipases erode surrounding tissues and lead to partial or complete anastomotic dehiscence and break-down of surrounding tissue. In addition, the leakage of pancreatic secretions, through a fistula in the pancreatico-enteric anastomosis can cause inflammation and auto-destruction of the peripancreatic and retroperitoneal tissues as well as the surrounding vessels and viscera. Subsequently, this can lead to delayed gastric emptying, biliary leakage, development of vascular erosions and hemorrhage, and lastly intra-abdominal abscesses. These may all lead to sepsis, shock, multiorgan failure, and death [3]. The incidence of POPF is reported to lie between 0% and 36% in older reports, but it tends to be much lower in high-volume centers and newer reports. Still, the most recent incidence of POPF after pancreatoduodenectomy is in the range of 20–25% [4–7]. The largest contributor to the postoperative mortality is due to these complications.

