Secondary 4	To evaluate the reliability and complications using microdialysis catheter CMA 65	Occurrence of catheter malfunction Occurrence of bleedings and infections	Daily check of the microdialysis catheter is functioning. Assessments of bleeding which affects circulatory parameter (development of circulatory shock or need of transfusion) and infection
Secondary 5	To evaluate patient quality of life and pain	Overall score and sub-scale scores of patient-reported questionnaires	Two patient-reported questionnaires: “Abdominal surgery impact scale” will be gathered with patient-reported McGill Pain Questionnaire-2 (SF-MPQ-2) preoperatively, at POD3 ± 1 day and at discharge ± 2 days from primary hospital + 30 and 90 days after surgery.
Secondary 6	To compare hospital costs of using microdialysisis versus “standard of care”	Number of Euros per patient undergoing PD based on microdialysis costs, length of stay (ICU and inpatient stay), reoperations, and postoperative complications	From medical records, procedures noted in electronic patient records, and radiological electronic patient records.
Exploratory	To compare other endpoints between patient with and without a microdialysis catheter	Hours from end of surgery to diagnosis of postoperative pancreatic AL (grades B and C).	Time as noted in electronic patient records.
		Total quantity (μg/mg) of vasoactive medications during surgery	Amount during surgery where the PD was performed. Derived from electronic patient records.
		Fluid balance - total iv volume administered and total diuresis	Diuresis and amount of fluid given iv during surgery and postoperatively until discharge from the hospital where the PD was performed. Derived from electronic patient records.
		Number of patients with biliary fistula	Biliary fistula defined according to the definition of the International Study Group of Liver Surgery (ISGLS). Graded into A, B, or C. From medical record, CT-scans.
		Number of patients with gastro-enteric AL	Gastro-enteric AL. From medical record, CT-scans.
		Pancreatic amylase and bilirubin concentrations in drainage fluid and in serum.	Analysis of drainage fluid and serum
		White blood cell count, C-reactive protein; concentrations	Laboratory data
		Number of patients with postoperative complications during total hospital stay in total and per complication	Defined by the modified Clavien-Dindo classification, from medical record, radiological examinations, and electronic patient records.

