### Assessment and management of patient based on microdialysis results

All patients in the intervention group with microdialysis glycerol > 400 μmol/ L during the first 48 h in three consecutive samples in the microdialysate will have an abdominal CT scan on POD 2. This examination will be reviewed by two senior radiologists allocated to this study and assessed according to the preexisting definitions of an abscess or radiologically visible anastomotic disruption. In the case of positive radiological findings, a subsequent CT scan will be performed according to algorithm (Fig. 1) and is described below. In the case where there is a clinical suspicion of an anastomotic leakage regardless of microdialysate values, an abdominal CT scan may be performed at the discretion of the surgeon at any time during the hospital stay, independent of microdialysate values. The CT scan will initially be assessed by the surgeon and the radiologist on call, but will also later be assessed independently by the two radiologists assigned to this study.

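### The protocol defines the cost endpoint in two conflicting ways, and one of them leaves out microdialysis-triggered scans that find no fistula

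*Protocol article*

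**What the plan says.** Two places in the protocol article state what the cost comparison contains.

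- **Objectives and endpoints, Table 1, Secondary 6.** The endpoint is "Number of Euros per patient undergoing PD based on microdialysis costs, length of stay (ICU and inpatient stay), reoperations, and postoperative complications". The sources are given as "From medical records, procedures noted in electronic patient records, and radiological electronic patient records".
- **Miscellaneous data to be collected.** The financial burden covers ICU stay, inpatient stay, readmissions, reoperations and, last in the list, "expensive) treatment procedures and examinations performed as a consequence of a POPF-development".

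The imaging rules are under Assessment and management of patient based on microdialysis results. That section requires a CT on postoperative day 2 for one group: "All patients in the intervention group with microdialysis glycerol > 400 μmol/ L during the first 48 h in three consecutive samples". The Ethical considerations section repeats this requirement for patients with a catheter. The algorithm starts treatment only if the scan confirms a leak, so it allows for negative scans. Apart from the trigger, where a leak is suspected clinically, "an abdominal CT scan may be performed at the discretion of the surgeon at any time during the hospital stay".

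**The concern.** A cost comparison needs the same counting rule in both arms, and the rule should not depend on an outcome that the intervention may change. The wording under Miscellaneous data meets neither condition cleanly. It costs an examination if it follows from a fistula, and fistula status is established after randomisation in a trial whose intervention is meant to change how and when a leak is found. A CT ordered because glycerol was high, which then shows no leak, does not follow from a fistula. Read literally, it is not costed. The protocol mandates such scans in one arm only.

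False alarms are among the costs of any monitoring method. If they are left out, a reported saving could come partly from the counting rule. Because the two lists also differ on readmissions and on microdialysis costs, two analysts following the same protocol could produce different cost results.

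**Working it through.** **Step 1. The two lists side by side.**

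| Item | Table 1, Secondary 6 | Miscellaneous data |
|---|---|---|
| ICU and inpatient stay | named | named |
| Reoperations | named | named |
| Readmissions | not named | named |
| Microdialysis costs | named | not named |
| Complications | all postoperative complications | not a separate item |
| Examinations and procedures | not named as an item; radiology and procedure records are sources | only if they follow from a fistula |

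The lists agree on stay and reoperations and differ on the other four rows.

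**Step 2. How a negative triggered CT is treated.** Under Miscellaneous data it is not costed, because no fistula developed. Under Table 1 it is neither a complication nor a reoperation. It counts only if microdialysis costs are taken to include scans that the monitoring sets off, which the table does not say.

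**Step 3. Scale, as an illustration only.** The protocol states no cost figure, unit price or scan rate, so there is nothing to reproduce.

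Inputs from the documents:
- Fistula incidence 20–25% (Background: "the most recent incidence of POPF after pancreatoduodenectomy is in the range of 20–25"%).
- 100 randomised per arm with about 15% not resected (Statistical considerations), so 100 × 0.85 = 85 operated.
- Assumed reduction in stay of 1.5 days (Statistical considerations).

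Assumptions, not in the documents:
- 5–30% of fistula-free intervention patients have one negative triggered CT.
- The rate of negative scans in fistula-free controls is 0–30%.
- One CT costs 0.1–1 bed-day.

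Net uncosted scans per patient = (1 − fistula rate) × (negative-scan rate, intervention − negative-scan rate, control).

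- No negative scans in controls, low end: 0.75 × 0.05 = 0.0375 per patient; × 85 = 3.2 scans.
- No negative scans in controls, high end: 0.80 × 0.30 = 0.24 per patient; × 85 = 20.4 scans.
- Equal rates in both arms: 0.
- 5% intervention against 30% control: 0.75 × (−0.25) = −0.19 to 0.80 × (−0.25) = −0.20 per patient.

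As a share of the value of the assumed 1.5-day saving, with no negative scans in controls: 0.0375 × 0.1 / 1.5 = 0.25% up to 0.24 × 1 / 1.5 = 16%.

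**The case against.** The strongest reply is that Table 1 is the endpoint definition and the other section only summarises data collection. Table 1 has no fistula condition, includes microdialysis costs and all complications, and draws on radiology records. A triggered CT can fairly be read as a microdialysis cost. The protocol also records "pre- and postoperative CT-scan results, mode of nutrition, and any transfusion requirements will also be recorded" without a fistula condition, and the Assessment Schedule (Table 2) follows the cost of complications to postoperative day 90. Detailed costing rules are often left to the full protocol or the analysis plan.

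Much of this stands, and it rules out three stronger readings that a reader might infer:

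- *That the plan costs examinations only after a fistula.* One of its two statements does so; the endpoint table does not.
- *That the cost difference must favour microdialysis.* Discretionary scans are open to both arms, and negative ones in controls would also go uncosted under the same wording. The calculation above gives zero or a reversed sign under some scan rates.
- *That Table 1 excludes readmissions.* It does not name them, but its inpatient stay is not limited to the first admission. Exclusion would be an inference from silence.

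The reply does not remove the conflict. The protocol states a rule that conditions costing on fistula development, and that rule differs from the endpoint table. This is contradictory text, not detail left for later. Naming radiology records as a source says where the data come from, not which scans are costed.

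**Conclusion.** The point holds as an inconsistency in the definition of a secondary endpoint, with a risk of bias attached. Under the Miscellaneous data wording, an intervention-specific cost is dropped and costing depends on a post-randomisation diagnosis. Bias in favour of microdialysis is plausible, because only the intervention arm has a mandated scan trigger, but the documents do not establish it.

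The size cannot be computed from the documents. On the assumed rates and prices the net omission runs from +0.24 scans per patient (intervention cost understated) through zero to −0.20 (control cost understated). With no negative scans in controls it is 0.25–16% of the value of the assumed 1.5-day saving. This is probably modest beside the cost of ICU and inpatient days, which both lists include. The primary endpoint is not affected. The text should be corrected before costs are analysed, but the trial does not depend on it.

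**What to change.** Replace both lists with one costing rule that applies identically to both arms:

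- Cost all ICU and inpatient days, readmissions, reoperations, postoperative imaging and procedures from the end of surgery to postoperative day 90, whatever the result and whether or not a fistula is diagnosed.
- Add microdialysis costs.
- State that negative scans triggered by microdialysis are included.
- Keep the denominator given in Table 1, patients undergoing pancreatoduodenectomy.

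No clinical rule changes. The cost is a change of wording and slightly more extraction from radiology and procedure records that Table 1 already names as sources. The cost result may turn out less favourable to microdialysis.

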### Microdialysis catheter and microdialysis analysis

Our research group has previously shown that microdialysis catheters with pore size for particles up to 100 kDa collect cytokines and complement factors, consequently, CMA 65 is used in this study [28]. The catheter is flexible and allows for the continuous monitoring and detection of local metabolic changes in the gastrointestinal tract. The catheter has a shaft length of 180 mm with a 30 mm membrane made of polyarylethersulfone. The diameter is 0.9 mm. The microdialysis catheter is tested for functionality before implantation. Before skin closure, the catheters will be implanted through a percutaneous hypodermic needle and affixed with an absorbable suture to surrounding connective tissue in close vicinity (< 1 cm) to the pancreaticojejunostomy. An epidermal suture will be used to minimize the risk of unintentional dislodgement. The catheters will be kept until the patient is discharged from the primary hospital or the catheter malfunctions.

The catheter is connected to a small battery-driven syringe pump (CMA 107, M Dialysis AB) and perfused by hydroxyethyl starch solution 130/0.4 (Voluven®, Fresenius Kabi AS, Halden, Norway) pumped at a rate of 1 μL/min as dialysis solution. The microdialysate will be collected in microvials which will be changed and analyzed hourly for metabolic parameters and cytokines. The samples thereafter will be analyzed for lactate, pyruvate, glucose, and glycerol with ISCUSflex Microdialysis Analyzer® (M Dialysis AB, Johanneshov, Sweden) by trained nurses/physicians in the following manner:
Every hour for the first 24 h.Thereafter, every 2 h as long as the microdialysis catheter still functions. With the exception of the initial 24 h, nighttime samples will be done at 0.00, 4.00, and 8.00 am.After POD 2 at 0.00 am: If the lactate/pyruvate-ratio increases > 50 combined with lactate > 4 mmol/L AND/OR glycerol increases > 400 μmol/L, the next two samples will be performed with an interval of 2 h (in place of every 4 h at night) to confirm or refute a pathological process.

Twice daily (≈ 08.00 am and 08.00 pm), samples from the microvials will be kept, and frozen to − 80 °C for later examination of cytokines and complement factors.

